### Sampling and evaluations

The sampling and examination schedule for follow-up is shown in Table 1. Evaluations are conducted at birth, 2 weeks, 3, 7, 13, 18, 24 and 30 months, and at 3, 5, and 8 years through home visits and scheduled visits at the ECUAVIDA outpatient clinic at HPAB. More detailed immunologic evaluations are performed in an immunology sub-cohort (ISC) of the last 295 infants recruited using blood samples collected at birth, 7, 13 and 24 months, and at 3, 5 and 8 years. A surveillance sub-cohort of 195 newborns living within the town of Quinindé are being followed-up actively and sampled for viral respiratory tract infections (influenza viruses, respiratory syncytial viruses, adenoviruses, and rhinoviruses) using nasal swabs and diarrheal illnesses (rotavirus and norovirus) using stool samples during the first 2 years of life. Aliquots of all stool samples collected and hypopharyngeal swabs (at routine sampling times) are being stored for future analyses of bacterial microbiota.

**Table 1 T1:** Sampling schedule for ECUAVIDA cohort

Visit	Ante-natal	Birth	< 2 wks	3 mths	7 mths	13 mths	24 mths	3 years	5 yrs	8 yrs
**Site**	**HPAB**	**HPAB**	**Home**	**HPAB/home**	**HPAB/home**	**Home**	**HPAB/home**	**HPAB/home**	**HPAB/home**	**Home**

Child										
Questionnaire		X	X		X	X	X	X	X	X
Faeces		X	X	X	X	X	X	X	X	X
Blood		X^a^	X		X	X	X	X	X	X
Clinical exam		X	X		X	X	X	X	X	X
Anthropometry		X			X		X	X	X	X
SPT							X	X	X	X
PFTs/BHR										X
Mantoux test										X

Mother										
Questionnaire	X	X	X	X						
Faeces	X	X	X							
Blood	X									
SPT										

Father										
Faeces			X	X						
SPT										

Household										
GPS			X^b^			X^b^				
Dust			X^b^							
Faeces			X							

Stool samples are collected also at 18 and 30 months. HPAB-Hospital Padre Alberto Buffoni in Quinindé, Esmeraldas Province; SPT-allergen skin test reactivity; PFTs-pulmonary function tests measured by spirometry; BHR-bronchial hyperresponsiveness or evidence of reversibility following β_2 _agonist; GPS-geographic positioning system measurements for mapping of households. ^a ^immunology sub-cohort only. ^b ^measurements repeated for change of address.

### Vaccination schedule

All vaccines are provided free of charge by the Ministry of Public Health at the vaccination clinic at HPAB. The vaccination schedule is: birth-BCG; 2 months and 4 months-pentavalent (Quinvaxem [DPT-HepB-Hib], Novartis), trivalent oral poliovirus vaccine (Chiron), rotavirus (Rotarix, GSK); 6 months-pentavalent, OPV; 12 months-measles-mumps-rubella (Serum Institute of India [SII]); and 18 months-DT (SII) and OPV.

### Measurement and definition of geohelminth exposures

Stool samples to measure geohelminth infections have been collected from mothers in the third trimester of pregnancy (stool samples collected after birth and before the child is 14 days old are considered to represent a third trimester stool sample where the mother has not received anthelmintic treatment) and from infants at 3, 7, 13, 18, 24, and 30 months, and at 3, 5, and 8 years. Stool samples are analysed using a combination of standard methods including direct saline mounts, the modified Kato-Katz method, formol-ether concentration, and carbon-coproculture methods [45]. Geohelminth infectious exposures will be defined as follows: 1) maternal geohelminth infections-presence of any geohelminth infection detected during the 3^rd ^trimester of pregnancy; and 2) infant geohelminth infections-presence of any geohelminth infections detected during the first 2 years of life.

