### Inclusion criteria

Although assessments and sampling are conducted during pregnancy, only a proportion of pregnant mothers attend antenatal clinics, and formal recruitment into the cohort occurs around the time of birth. Entry criteria into the study are: 1) healthy normal baby less than 14 days old; 2) at least one stool sample collected from the mother; 3) the family has lived in the District for the last 2 years and does not plan to move out of the District over the following 3 years; 4) the home is accessible; and 5) the mother is 17 years or older.

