### Study limitations

We expect losses to follow-up to be up to 10% in the first year (i.e. 2,163/2,403 followed up) and 5% annually to age 3 and a further 5% between ages 3 and 5. Estimates for the number of children followed-up are: 2 years-2,055, 3 years-1,952, and 5 years-1,854. Losses are due to the mobility of the study population.

Potential sources of biases are selection bias caused by losses to follow up and information bias caused by systematic misclassification of outcomes. The following methods are being used to minimize these biases: *Achieving high rates of follow-up *- a) we have a well-trained study team employed full-time for the cohort; b) we conduct regular home visits to maintain contact with study mothers; c) the universal use of mobile phones allows us to maintain regular contact with study mothers; d) the mother of each child is given a cohort identification card with a phone number to make appointments at the ECUAVIDA outpatient Clinic; e) changes of address are followed up actively with home visits to repeat environmental sampling. *Information bias *- a) repeated measurements of outcomes (for asthma, eczema, and allergen skin test reactivity) should reduce misclassification and recall bias; b) clear definitions for primary outcomes and exposures; c) evaluation of outcomes is being performed blind to exposure status. Detailed information on potential confounding factors is being collected.

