**Figure 2 F2:**
[figure not shown]
**Conceptual model for effects of maternal and infant geohelminth infections on vaccine immune responses measured at 7 months, 2 years or 5 years**. Maternal infections would be expected to mediate effects on vaccine responses at 7 months and 2 years, although infant infections, generally acquired during the second year of life, may contribute to effects at 2 years. The suppressive effects of infant infections would be expected to be most important at 5 years. Potential immunological mechanisms that may mediate the suppressive effects of geohelminth exposures are shown in dashed boxes.

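### Both primary exposures are any-detection rules applied to unequal numbers of stools, with no allowance for how many stools were examined

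*Protocol article*

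**What the plan says.** Under Measurement and definition of geohelminth exposures, the maternal exposure is "maternal geohelminth infections-presence of any geohelminth infection detected during the 3^rd ^trimester of pregnancy" and the infant exposure is "infant geohelminth infections-presence of any geohelminth infections detected during the first 2 years of life". Neither rule refers to how many stools were examined.

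**Mothers.** The Inclusion criteria require "at least one stool sample collected from the mother" and note that "only a proportion of pregnant mothers attend antenatal clinics". Table 1 schedules maternal faeces at the antenatal visit, at birth and before 2 weeks. For an untreated mother, "stool samples collected after birth and before the child is 14 days old are considered to represent a third trimester stool sample".

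**Infants.** Stools are collected "from infants at 3, 7, 13, 18, 24, and 30 months, and at 3, 5, and 8 years". Five of these fall in the 2-year window. Table 1 also marks child faeces at birth and before 2 weeks, so up to seven are possible. No minimum is stated. The legend of Figure 2 describes "infant infections, generally acquired during the second year of life".

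**Outcomes.** Eczema needs at least one qualifying presentation in 3 years, assessed at 7, 13, 24 and 36 months and at clinic attendances. Asthma needs current wheeze plus either wheeze reported at the 13-, 24- or 36-month assessments or an earlier study-clinic diagnosis.

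**Bias.** Study limitations names loss to follow-up and misclassification of outcomes. Its repeated-measurement safeguard covers outcomes only. For exposures it relies on clear definitions.

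**The concern.** Under an any-detection rule, each further stool is another chance to become exposed and none can reverse the label. Two people with the same true infection history can be labelled differently because one gave more stools. This has two consequences.

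- **Dilution.** Infections that are missed stay in the unexposed group, and the contrast shrinks towards no effect. This applies to both exposures.
- **Shared visits.** For infant exposure, some of the visits that yield stools also yield the eczema and early-wheeze records. A child seen less often has fewer chances to be labelled exposed and fewer chances to be recorded as a case. That links exposure and outcome positively even with no true effect, which opposes the protection the study expects. Blind outcome assessment does not remove it.

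The shared-visit argument concerns eczema and asthma. Skin test reactivity at 5 years and the antibody outcomes are read at set time points, so this mechanism does not arise there in the same way.

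**Working it through.** **1. The plan's own figures.** Table 2, asthma at 5 years: N = 1,725, 17% vs 23%, α = 0.05 (taken as two-sided).

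Power = Φ{[|p1 − p0| − z√(p̄(1 − p̄)(1/n1 + 1/n0))] / √(p1(1 − p1)/n1 + p0(1 − p0)/n0)}

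- Maternal (50% exposed): 87.7%, or 86.4% with continuity correction; stated 86%.
- Infant (35% exposed): 84.1%, or 82.5% with correction; stated 83%.
- Odds ratio: (0.17/0.83)/(0.23/0.77) = 0.686.

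The stated power reproduces, so these rows are a sound base.

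**2. Detection by number of stools.** Per-stool sensitivity s is not in the document. Assume 0.5 to 0.8 and independent stools, so cumulative sensitivity is S = 1 − (1 − s)^k.

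- Mothers: S is 50–80% with one stool and 87.5–99.2% with three. At 50% true prevalence, the infected share of test-negative mothers is 0.5(1 − S)/[0.5(1 − S) + 0.5]. This gives 33–17% with one stool and 11–1% with three.
- Infants: take the Table 2 note's 30% as the yield of all five stools. With equal yield per stool, the labelled share is 1 − 0.7^(k/5): 6.9%, 13.3%, 19.3%, 24.8% and 30% for one to five stools. If instead 70% of first detections come at 18 or 24 months (assumption), a child missing both is labelled exposed with chance 0.30 × 0.30 = 9%.

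**3. Dilution.** Take the Table 2 exposure prevalence T as true, overall sensitivity se and perfect specificity. Then the labelled share is T·se, and the unexposed risk is [T(1 − se)p1 + (1 − T)p0]/(1 − T·se).

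| se | Maternal asthma OR | Power | Infant asthma OR | Power |
|---|---|---|---|---|
| 1.0 | 0.686 | 87.7% | 0.686 | 84.1% |
| 0.9 | 0.707 | 80.7% | 0.698 | 78.0% |
| 0.8 | 0.726 | 72.4% | 0.709 | 70.9% |
| 0.7 | 0.743 | 63.1% | 0.719 | 62.8% |
| 0.6 | 0.757 | 53.3% | 0.729 | 54.0% |

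**4. Shared visits, no true effect.** Assumptions: 20–30% of analysed children miss the 18- and 24-month stools (labelled 9% rather than 30%), and their asthma is recorded at 80% or 60% of the 20% expected in fully seen children.

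Worked case, 20% incomplete and 80% recording (risk 16%):
- labelled exposed: 0.8 × 0.30 + 0.2 × 0.09 = 0.258
- risk if exposed: (0.8 × 0.30 × 0.20 + 0.2 × 0.09 × 0.16)/0.258 = 0.1972
- risk if unexposed: (0.8 × 0.70 × 0.20 + 0.2 × 0.91 × 0.16)/0.742 = 0.1902
- OR = (0.1972/0.8028)/(0.1902/0.8098) = 1.05

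With 60% recording the OR is 1.10. With 30% incomplete it is 1.07 (80% recording) and 1.14 (60%).

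The sign depends on how stool count relates to recorded outcome. With half the children at five stools and half at two (30% and 13.3% labelled), the null OR is 1.00 if risk is 20% in both groups. It is 1.10 if risk is 23% (five stools) vs 17% (two), and 0.91 if those risks are reversed.

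**5. Check of remedies.** Within a stratum of children with the same stools examined and the same recorded risk, labelled-exposed and unexposed children have equal risk under the null. The stratified OR in step 4 is therefore 1.00.

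Reducing every mother to one stool does the opposite of what is wanted. For eczema (N = 1,840, 25% vs 35%, α = 0.01, planned OR 0.62), let half the mothers give one stool and half three, with s = 0.7. Mean sensitivity is (0.70 + 0.973)/2 = 0.8365, giving OR 0.66 and power 92%. With one stool each, the OR is 0.69 and power 81%. At s = 0.5, power falls from 80% to 55%.

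**The case against.** A reader might infer that people with few stools are classed as uninfected. The document does not say so: one positive stool makes anyone exposed, and fewer stools only raise the chance of a false negative. Nor does it say that a child who missed the 18- and 24-month stools is coded unexposed rather than missing. A child with no stool at all is neither described nor excluded. A full protocol or analysis plan may hold such a rule, and its absence from an article is not in itself a fault.

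Other points limit the effect:
- Several stool methods are combined per sample.
- An accessible home is an entry criterion, visits can take place at home, and contact is actively maintained.
- Expected losses are moderate ("We expect losses to follow-up to be up to 10% in the first year"; 2,055 of 2,403 expected at 2 years).
- A stool after birth may simply replace a missed antenatal one, so how many mothers gave more than one is unknown.
- The listed confounders are given as an example, so silence on stool count there proves little.

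It is also tempting to argue that antenatal attendance drives both maternal stool count and outcome recording. Nothing in the document supports that link, so for mothers only dilution is claimed here.

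What stands is that the article states the operative definition of both primary exposures, relies on clear definitions as its protection against information bias, and ties part of the outcome record to the visits that supply infant stools. That is more than detail left to another document.

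**Conclusion.** The concern holds in limited form. As written, the chance of being labelled exposed rises with the number of stools examined, and that number can differ between participants. Dilution towards no effect follows wherever infections are missed. For infant exposure with eczema or asthma, shared visits can also push the odds ratio upward.

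The size is unknown. Per-stool sensitivity and stool completeness are not reported, and every figure beyond the reproduced power rests on assumed values. Within those ranges, dilution could cost substantial power in the asthma rows, while the shared-visit distortion is small to moderate: a null OR of about 1.05 to 1.14, against a planned OR of 0.69. If stool count is unrelated to recorded outcome, no false association arises. A reader should not conclude that the primary contrasts are biased, only that the definition leaves them open to it.

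**What to change.** Keep the any-positive definition for both exposures and state three additions in the analysis plan:

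1. In every primary model, adjust for or stratify by the number of stools examined in the exposure window. For infants, also include whether the 18- and 24-month stools were examined.
2. Add a sensitivity analysis restricted to participants with a complete, or pre-set minimum, set of stools. Apply the restriction equally to positives and negatives.
3. Report the distribution of stools examined by exposure label.

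Two alternatives should be avoided. Reducing mothers to one stool discards information and lowers power. Setting only incompletely sampled negatives to missing keeps their positive counterparts, so every observed exposure among incompletely sampled children would be positive.

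The cost is a change of analysis wording, provided the number of stools examined per participant is on record; no new samples are needed. Intervals will be slightly wider and the sensitivity analysis smaller. Adjustment addresses the distortion from unequal sampling but does not fully remove dilution by false negatives.

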### Measurement and definitions of study outcomes

#### Primary study outcomes

1. *Vaccine immune responses: *vaccine immunity will be measured by the presence of protective antibody levels measured as follows-1) IgG to tetanus toxoid as described previously [46]. Immune protection will be defined > 0.15 IU/ml; 2) titer of neutralizing antibodies to OPV type 3 using the microneutralization assay at the Health Protection Agency (HPA), London, UK. Protection will be defined as OPV type 3 virus neutralization at 100TCID50 at serum dilution ≥ 1:8 dilution; 3) IgA to rotavirus (HPA); protection indicated by titers ≥ 20 U/mL; 4) IgG to polyribosylribitol phosphate of *Haemophilus influenzae *type B (Binding site, Birmingham, UK); protection > 0.15 mg/mL; 5) anti-HBS IgG antibodies (Architect, Abbott Diagnostics, Sligo, Ireland), protection > 10 IU/mL IgG. Plasma samples collected at 24 months and 5 years will be used to measure short-term (24 months) and long-term (5 years) antibody-mediated protective immunity. Vaccine responses to Hib and rotavirus will be measured only at 7 months to distinguish vaccine-mediated responses from those acquired from natural exposures to these infections.

2. *Atopy: *defined by the presence of allergen skin test reactivity at 5 years to any of the following aeroallergens: *Dermatophagoides pteronyssinus/farinae *mix, American cockroach (*Periplaneta americana*), fungi mix, dog, cat, and mixed grass pollen. A positive test is defined by the presence of a skin wheal ≥ 3 mm greater than saline control. All skin testing will be conducted by trained physicians and will be supervised by a highly experienced clinical investigator ([name]).

### Secondary study outcomes-immunological outcomes

Five possible mechanisms have been defined that could mediate the putative effects of geohelminth infections on the primary study outcomes. A justification for choosing these mechanisms is provided in the Discussion. The mechanisms are: 1) Th2 polarization-measured by the ratio of IL-5 to IFN-γ protein produced by peripheral blood leukocytes (PBLs); 2) immune homeostasis-production of IL-10 spontaneously in 5-day PBL cultures [50]; 3) immune suppression-antigen-specific suppression measured by frequencies of IL-10^+^CD4^+ ^T cells or IL-10 production by antigen-stimulated PBLs [51-53] or 'bystander suppression' measured by IL-10 production by *A. lumbricoides *antigen-stimulated PBLs [54,55]; 4) immune maturation-capacity of PBLs to produce IFN-γ to sub-optimal stimulus with Staphylococcal enterotoxin B (SEB); and 5) pro-inflammatory responses-IL-8 production by PBLs stimulated with LPS [56], and quantities of IL-17, IFN-γ, and IL-5 produced by SEB-stimulated PBLs. Flow cytometry experiments will be performed using cryopreserved and fixed peripheral blood leukocytes using standardized protocols [41,56,57].

### For each of the outcomes, the following mechanisms will be evaluated

1. *Vaccine immunity*: Immunological outcomes will be measured at 24 months (short-term immunity) and 5 years (long-term immunity) for Th2 polarization (tetanus toxoid [TT] and tuberculin [PPD]-stimulated PBLs), immune homeostasis, and immune suppression (IL-10 production by PBLs stimulated with TT, PPD, and *A. lumbricoides *antigen).

2. *Atopy*: Immunological outcomes will be measured at 5 years for immune homeostasis and immune suppression (frequencies of IL-10+CD4+ T cells [ISC only] or IL-10 production by PBLs stimulated with *D. pteronyssinus, P. americana*, and *A. lumbricoides *antigen).

3. *Eczema: *Immunological outcomes will be measured up to 3 years for markers of immune maturation, immune homeostasis, immune suppression (frequencies of IL-10^+^CD4^+ ^T cells (ISC only) or IL-10 production by *A. lumbricoides*-stimulated PBLs), and pro-inflammatory responses (ISC only).

4. *Asthma*: Immunological outcomes will be measured at 5 years for markers of immune homeostasis, immune regulation/suppression (frequencies of IL-10^+^CD4^+ ^T cells [ISC only] and IL-10 production by PBLs stimulated with *D. pteronyssinus *and *A. lumbricoides *antigen), Th2 polarization (ratio of IL-5 to IFN-γ to sub-optimal SEB stimulus), and pro-inflammatory responses (ISC only).

### Study limitations

We expect losses to follow-up to be up to 10% in the first year (i.e. 2,163/2,403 followed up) and 5% annually to age 3 and a further 5% between ages 3 and 5. Estimates for the number of children followed-up are: 2 years-2,055, 3 years-1,952, and 5 years-1,854. Losses are due to the mobility of the study population.

Potential sources of biases are selection bias caused by losses to follow up and information bias caused by systematic misclassification of outcomes. The following methods are being used to minimize these biases: *Achieving high rates of follow-up *- a) we have a well-trained study team employed full-time for the cohort; b) we conduct regular home visits to maintain contact with study mothers; c) the universal use of mobile phones allows us to maintain regular contact with study mothers; d) the mother of each child is given a cohort identification card with a phone number to make appointments at the ECUAVIDA outpatient Clinic; e) changes of address are followed up actively with home visits to repeat environmental sampling. *Information bias *- a) repeated measurements of outcomes (for asthma, eczema, and allergen skin test reactivity) should reduce misclassification and recall bias; b) clear definitions for primary outcomes and exposures; c) evaluation of outcomes is being performed blind to exposure status. Detailed information on potential confounding factors is being collected.

### Study power

The study sample size is fixed at 2,403 newborns. Primary outcome variables will be treated as statistically independent. Power calculations for primary study questions are shown in Table 2[58,59]. We expect a high degree of power for the estimation of most primary and secondary study outcomes (≥ 80% depending on immunological mechanism at α = 0.01) that will allow for the loss of power expected by controlling for confounding.

**Table 2 T2:** Power for analysis of primary exposure-outcome associations

Primary exposures (geohelminth infections)	Outcome	Sample size available	Analysis sample size	Exposure prevalence	Expected prevalence of outcomes (exposed vs. unexposed groups)	Α	Power
Maternal	Vaccine antibodies @ 7 mths						
	Hib	2,300	1,000	50%	65% vs. 75%	0.01	80%
	Rotavirus	2,300	1,000	50%	40% vs. 60%	0.01	> 99%
Maternal	Vaccine antibodies @ 2 yrs						
	TT	1,955	1,000	50%	85% vs. 95%	0.01	> 99%
	HBV	1,955	1,750	50%	80% vs. 85%	0.05	80%
	OPV type 3	1,955	500	50%	80% vs. 95%	0.01	> 99%
Infant	Vaccine antibodies @ 5 yrs						
	TT	1,725	1,000	35%	60% vs. 80%	0.01	99%
	HBV	1,725	1,500	35%	70% vs. 80%	0.01	95%
	OPV type 3	1,725	1,000	35%	50% vs. 70%	0.01	> 99%

Maternal	SPT @ 3 years	1,840	1,840	50%	15% vs. 25%	0.01	99%
Infant	SPT @ 3 years	1,840	1,840	35%	15% vs. 25%	0.01	> 99%

Maternal	Eczema @ 3 years	1,840	1,840	50%	25% vs. 35%	0.01	99%

Maternal	Asthma @ 5 years	1,725	1,725	50%	17% vs. 23% #	0.05	86%
Infant	Asthma @ 5 years	1,725	1,725	35%	17% vs. 23% #	0.05	83%
Infant	Asthma @ 5 years	1,725	1,207	20%	25% vs. 15% #	0.01	93%

Random samples of the study population will be selected for analysis of the protective levels of vaccine antibodies. Based on data from the cohort we estimate that 20% of children will have allergen skin test reactivity to any allergen at 5 years, that 30% of children will have at least one documented episode of eczema by 3 years of age and that 20% of children will have asthma at 5 years. Based on data from the cohort we estimate that ~50% of mothers are infected with any geohelminth parasite and ~30% of children will have at least one documented geohelminth infection during the first 2 years of life.

#-expected effects of geohelminth infections on asthma prevalence using data from cross-sectional analyses in Ecuador [58] and Brazil [59].

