### Analysis plan

Statistical analysis will be guided by the conceptual frameworks presented for each of the study outcomes (Figures 2, 3, 4 and 5). The analysis of the primary study outcomes will use multiple logistic regression to estimate the Odds Ratios for exposure-outcome associations with adjustment for appropriate confounding factors. For example, *a priori *confounders for the association between maternal geohelminth infections and eczema by 3 years of age are gender, maternal educational level, household crowding, and infant geohelminth infections. The primary analyses will evaluate the effects of maternal geohelminth infections or infant geohelminth infections on: 1) protective immunity to common childhood vaccines: 2) the presence of allergen skin test reactivity at 5 years of age; 3) the development of eczema by 3 years of age; and 4) the development of asthma at 5 and 8 years of age. Immunological variables will be defined as binary variables with a cut-off defined by the limit of detection of the assays (i.e. IL-10) or median level (i.e. IL-8) or as log_e_-transformed continuous variables. Because immunological variables are considered as intermediate in the causal pathways between exposures and outcomes, these variables will be evaluated in hierarchical analyses [60].

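### Table 2 gives unadjusted powers, so the stated allowance for confounder control does not exist for Hib at 7 months or hepatitis B at 2 years and is thin for infant-exposure asthma

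*Protocol article*

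**What the plan says.** The Study power section of the protocol article fixes the sample at 2,403 newborns and refers to Table 2. It then states: "We expect a high degree of power for the estimation of most primary and secondary study outcomes". A parenthesis gives at least 80% at α = 0.01, depending on immunological mechanism, and the sentence ends by saying that this is power "that will allow for the loss of power expected by controlling for confounding".

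Each row of Table 2 lists an available and an analysed sample size, an exposure prevalence, two outcome prevalences, α and power. There is no term for covariates. The rows at issue read:

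- Hib, 7 months, maternal exposure: "Hib 2,300 1,000 50% 65% vs. 75% 0.01 80"
- HBV, 2 years, maternal exposure: "HBV 1,955 1,750 50% 80% vs. 85% 0.05 80"
- Asthma, maternal exposure: "Asthma @ 5 years 1,725 1,725 50% 17% vs. 23% # 0.05 86"
- Asthma, infant exposure: "Asthma @ 5 years 1,725 1,725 35% 17% vs. 23% # 0.05 83"
- Asthma, third row: "Asthma @ 5 years 1,725 1,207 20% 25% vs. 15% # 0.01 93"

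The Analysis plan section specifies "multiple logistic regression to estimate the Odds Ratios for exposure-outcome associations with adjustment for appropriate confounding factors". The note under Table 2 puts infant infection in the first two years at about 30%, while the infant rows for vaccines, skin tests and the second asthma question use 35%.

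**The concern.** When an exposure is correlated with the confounders in the model, its adjusted effect is estimated less precisely than its crude effect. The article expects this loss and says that the tabulated power covers it. A row printed at exactly 80%, the only threshold that the section names, has nothing left to give up.

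The risk lies in interpretation. The sentence does not say which outcomes fall outside its scope. A null adjusted result for Hib, 2-year HBV or infant-exposure asthma could be read as coming from a comparison with power in hand, when the table leaves little or none. The α of 0.01 in the sentence adds to this, because some rows reach 80% only at 0.05.

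**Working it through.** **Inputs.** N, exposure prevalence e, outcome prevalences p1 and p2, and α come from Table 2. Sidedness is not stated; two-sided is assumed because it reproduces the table. R², the share of exposure variance explained by the confounders, is not in the article. It is assumed at 0.05, 0.10 and 0.20.

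**Formula.** With n1 = N·e, n2 = N·(1−e) and p̄ the pooled prevalence:

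z = [|p1−p2| − c − z(1−α/2)·√(p̄(1−p̄)(1/n1+1/n2))] / √(p1(1−p1)/n1 + p2(1−p2)/n2), and power = Φ(z).

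Here c = 0 without continuity correction and c = ½(1/n1+1/n2) with it.

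**Reproducing the printed figures.** For Hib, n1 = n2 = 500 and p̄ = 0.70. The null standard error is 0.02898, the alternative standard error 0.02881, and the critical value 2.5758.

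- Without correction: (0.10 − 2.5758×0.02898)/0.02881 = 0.880, power 81.1%.
- With correction, c = 0.002: z = 0.810, power 79.1%.

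| Row | Printed | Without / with correction |
|---|---|---|
| Hib, 7 months | 80% | 81.1 / 79.1% |
| HBV, 2 years | 80% | 78.6 / 76.8% |
| Asthma, maternal | 86% | 87.7 / 86.4% |
| Asthma, infant, 35% exposed | 83% | 84.1 / 82.5% |
| Asthma, third row, 20% exposed, α 0.01 | 93% | 84.3 / 82.2% |

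The first four rows agree with the print to within two points on the uncorrected version, as do the nine rows not shown. The table therefore holds unadjusted two-group powers. The fifth row does not reproduce. Changing its α to 0.05 gives 93.0% with correction; keeping α = 0.01 but setting exposure to 30% gives 92.8% without correction. The article does not show which entry is off.

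**Adjusted power.** N is replaced by N·(1−R²). Each cell runs from with to without correction.

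| Row | R² 0.05 | R² 0.10 | R² 0.20 |
|---|---|---|---|
| Hib (N = 1,000) | 76-79% | 74-76% | 67-70% |
| HBV, 2 years (N = 1,750) | 75-77% | 72-74% | 67-69% |
| Asthma, maternal | 85-86% | 82-84% | 78-80% |
| Asthma, infant, 35% | 80-82% | 78-80% | 73-75% |
| Asthma, third row | 80-82% | 77-80% | 71-74% |

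**Largest R² that keeps 80%** (without / with correction):

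- Hib: about 0.02 / none
- 2-year HBV: none / none
- Maternal asthma: 0.19 / 0.15
- Infant asthma, 35%: 0.10 / 0.06
- Third asthma row: 0.10 / 0.05
- Each of the other nine rows: about 0.35 or more

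**Exposure prevalence.** With the note's 30% in place of 35%, the infant asthma row starts at 80.9 / 79.0% before any adjustment.

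**Significance level.** At α = 0.01, unadjusted and without correction, 2-year HBV has 57.0%, maternal asthma 70.6% and infant asthma (35%) 64.1%.

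**Sample needed for 80%.**

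- Hib: 1,087 / 1,131 at R² 0.10 and 1,223 / 1,273 at R² 0.20, all within the 2,300 available.
- 2-year HBV: about 1,907 / 1,990 at R² 0.05, 2,012 / 2,100 at 0.10 and 2,264 / 2,363 at 0.20, against 1,955 available. Assaying all 1,955 gives 82.9 / 81.4% unadjusted, 81.0 / 79.3% at R² 0.05 and 78.9 / 77.0% at R² 0.10.

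**The case against.** The sentence is hedged: it speaks of most outcomes, and nine of the 14 rows would survive heavy adjustment. It promises no power threshold after adjustment, and its parenthesis ties the 80% to the immunological mechanism, which points at least partly to secondary outcomes. Crude power with a remark on headroom is common in a condensed cohort article with a fixed sample. No exposure-confounder association is reported, so every adjusted figure is conditional on an assumption.

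Most of this stands, and it rules out three stronger readings that a reader might infer:

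- That the allowance statement is false as a whole. The word most, and the nine rows with reserve, do not support that.
- That asthma in general has little or no margin. The maternal row tolerates R² up to about 0.15-0.19, and the third row is printed at 93%; its reserve looks thin only because that figure does not reproduce.
- That 2-year HBV can only be restated. On the uncorrected calculation, assaying all 1,955 keeps 80% at R² 0.05.

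What the objection does not remove is that the sentence names no exceptions. Two primary questions sit exactly at 80% with nothing to absorb a loss that the article itself expects. For those two rows the conclusion hardly depends on R²: Hib tolerates about 0.02 at most and HBV none. Nor is this a detail left to a fuller document, since the article makes the statement and prints the table beside it.

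**Conclusion.** The point holds in a limited form.

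- **No allowance:** Hib at 7 months and HBV at 2 years.
- **Thin allowance:** infant-exposure asthma at 35%, lost at an R² of about 0.06-0.10 and essentially absent from the start at 30% exposure.
- **Modest allowance:** maternal asthma.
- **Ample allowance:** nine of 14 rows.

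Two related errors belong with it. The sentence cites α = 0.01 although 2-year HBV and both 17% versus 23% asthma rows rely on 0.05. The third asthma row's 93% does not follow from its printed inputs.

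The unadjusted figures assume two-sided tests. The adjusted figures also assume R² between 0.05 and 0.20 and the usual approximation that effective sample size is N·(1−R²). They show sensitivity and are not estimates for this cohort.

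**What to change.** 1. Limit the allowance statement to the rows that have reserve, and name those that do not.
2. Label Table 2 as unadjusted, make the α in the sentence agree with the α in each row, correct the third asthma row, and use one infant exposure prevalence in table and note.
3. Give power for the adjusted model with R² estimated from cohort data. If R² has to be assumed, show a range. For 0.05-0.20 that is Hib 67-79%, 2-year HBV 67-77% at N = 1,750, infant asthma 73-82% and maternal asthma 78-86%.
4. For Hib, assay about 1,090-1,280 of the 2,300 available 7-month samples instead of 1,000. The lower figure holds 80% at R² 0.10 without continuity correction, the upper at R² 0.20 with it.
5. For 2-year HBV, either assay all 1,955 or restate the power.

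**Cost.** Items 1 to 3 are text, plus one regression of exposure on the confounders. Item 4 costs about 90-280 extra Hib assays on plasma already collected. Item 5 costs 1,955 − 1,750 = 205 extra HBV assays, or only a restated figure. No new enrolment is needed.
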